### Intervention Fidelity

For purposes of the present study, a random selection of 20% of Quitlink intervention participants will be made, and routinely recorded calls will be rated for fidelity to the treatment manual by an independent rater using a checklist derived from the treatment manual which includes core behavior change techniques (BCTs) relevant to smoking cessation. BCTs are defined as the smallest identifiable components of an intervention that in themselves have the potential to change behavior (39).

### Concurrent Treatment

In both the Standard Smoking Care and Quitlink Intervention conditions, participants will be able to partake of any interventions initiated by themselves or their health providers during the course of the study and these will be monitored at the follow-up assessments.

### Outcome Measures

Outcome measures will be assessed at 2-, 5-, and 8-months post baseline, by telephone. These will be conducted by independent assessors who will remain blind to intervention allocation. Outcome measures will all be assessed before any process measures where answers could suggest experimental condition. All assessment instruments are widely used in mental health and/or tobacco treatment research and practice (see Table 1) and cover the domains hypothesized to be impacted upon by the intervention.

**Table 1 T1:** Assessment schedule.

**Assessments**	**Baseline**	**2 month**	**5 month**	**8 month**
***Demographic characteristics***	X			
**MENTAL ILLNESS DIAGNOSIS**				
Self-report -Have you ever received a mental health diagnosis? -Have you ever been diagnosed with a psychotic disorder?	X			
MINI (diagnostic interview)		X	^*^	^*^
McLean screening instrument for borderline personality disorder		X	^*^	^*^
**MEDICATIONS**				
Current medications	X/E			
Medication side effects	X			
**SMOKING MEASURES:**				
Current smoking and quit attempts	X	X	X	X
7 day point prevalence abstinence (self-reported)		X	X	X
6 month prolonged abstinence (primary outcome)				X
CO Monitoring (those reporting abstinence)				A
Heaviness of Smoking Index	X	S	S	S
Tobacco types	X			
Cost	X	S	S	S
History (age first smoked)	X			
Social influences	X			
Cravings	X	X	X	X
Smoking use motives	X			
Situations not allowed to smoke		X	X	X
Goal	X			
Motivation to quit	X	S	S	S
Confidence to quit	X			
Self-efficacy		X	X	X
Products/services to help quit (including NRT, Quitline)	X	X	X	X
Nicotine replacement products (helpfulness, likely use)	X			
Counseling preference (in person or telephone)	X			
Minnesota Nicotine Withdrawal Scale (only two items in follow ups)	X	X	X	X
**MENTAL HEALTH:**				
Kessler-10	X	X	X	X
**SUBSTANCE USE:**				
Alcohol (AUDIT-C)	X	X	X	X
Cannabis use with tobacco question	X	X	X	X
Cannabis (First question of CUDIT-R)	X	X	X	X
**QUALITY OF LIFE:**				
AQoL-8D	X	X	X	X
**MEDICATIONS—NRT/CESSATION:**				
Process measure (i.e., provided to intervention participants)		E		
***Perceived support—***GP, Psychiatrist, other health professional		X		
**QUITLINE USE:**				
Number, length, content and timing of calls		E		
**SERVICE USE**				
Hospitalizations and other intensive health service use		X		X
Time off from work and usual duties		X	X	X
Financial stress questions	X	X	X	X
**Therapeutic Alliance:**		X		
WAIT-3		X^$^		
Peer worker brief intervention question		X		
**Qualitative interviews**		I	I	I
**PBS/MBS cost data**				E

*AUDIT-C, Alcohol Use Disorders Identification Test – Brief (40); AQoL-8D, Assessment of Quality of Life-8D (41); CUDIT-R, Cannabis Use Disorders Identification Test – Revised (42); CO, Carbon monoxide; GP, General Practitioner; Kessler-10, Kessler Psychological Distress Scale (43); MINI, Mini International Neuropsychiatric Interview (44); NRT, Nicotine Replacement Therapy; WAIT-3, Working Alliance Inventory for Tobacco-−3 (45); MBS, Medicare Benefits Schedule; PBS, Pharmaceutical Benefits Scheme*.

**Key**

* *If not captured at previous assessment*.

***E** Extracted data*.

***S** Current smokers*.

***$** If used Quitline*.

***A** Those reporting abstinence*.

***I** Selected subsample*.

#### Primary Outcome

The primary outcome is defined as continued abstinence from smoking since the end of the treatment period, i.e., 6 months sustained abstinence, with no relapse (defined as 7+ days of continuous smoking, and no reported smoking in the last week), with biochemical verification at 8-month follow-up. Sustained abstinence will be assessed via the following question: “When did you last smoke a cigarette, even a puff?” If a participant reports prolonged abstinence at the 8 month follow up, and no smoking in the last week, they will be asked to attend a face to face visit to complete CO testing for objective validation using a Micro+ Smokelyzer, with a reading of 8 ppm or higher defined as indicative of recent smoking.

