## Abstract

**Introduction:** Although smokers with severe mental illnesses (SSMI) make quit attempts at comparable levels to other smokers, fewer are successful in achieving smoking cessation. Specialized smoking cessation treatments targeting their needs can be effective but have not been widely disseminated. Telephone delivered interventions, including by quitlines, show promise. However, few SSMI contact quitlines and few are referred to them by health professionals. Mental health peer workers can potentially play an important role in supporting smoking cessation. This study will apply a pragmatic model using peer workers to engage SSMI with a customized quitline service, forming the “Quitlink” intervention.

**Methods:** A multi-center prospective, cluster-randomized, open, blinded endpoint (PROBE) trial. Over 3 years, 382 smokers will be recruited from mental health services in Victoria, Australia. Following completion of baseline assessment, a brief intervention will be delivered by a peer worker. Participants will then be randomly allocated either to no further intervention, or to be referred and contacted by the Victorian Quitline and offered a targeted 8-week cognitive behavioral intervention along with nicotine replacement therapy (NRT). Follow-up measures will be administered at 2-, 5-, and 8-months post-baseline. The primary outcome is 6 months continuous abstinence from end of treatment with biochemical verification. Secondary outcomes include 7-day point prevalence abstinence from smoking, increased quit attempts, and reductions in cigarettes per day, cravings and withdrawal, mental health symptoms, and other substance use, and improvements in quality of life. We will use a generalized linear mixed model (linear regression for continuous outcomes and logistic regression for dichotomous outcomes) to handle clustering and the repeated measures at baseline, 2-, 5-, and 8-months; individuals will be modeled as random effects, cluster as a random effect, and group assignment as a fixed effect.

**Discussion:** This is the first rigorously designed RCT to evaluate a specialized quitline intervention accompanied by NRT among SSMI. The study will apply a pragmatic model to link SSMI to the Quitline, using peer workers, with the potential for wide dissemination.

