### Sample Size Determination

Based on our previous study (23) which achieved a 15% prolonged abstinence rate in depressed smokers, and knowing rates are considerably less among those with more severe mental illnesses (62) we anticipate that for the primary outcome of prolonged abstinence at 8 months, prolonged abstinence will occur in 1% of the control arm vs. 8% in the intervention arm. To detect this effect with 80% power at *p* = 0.05, we require 134 per arm. We expect ~30% attrition, inflating the sample size to 191/arm or 382 overall. Thus, we will recruit 382 smokers over 36 months and follow up at 2-, 5-, and 8-months post-baseline, completing the study over a 4.5-year period.

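### The primary outcome allows short lapses under a 7-day relapse rule, but the one question named to measure it records only the last puff and cannot apply that rule

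*Protocol article*

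**What the plan says.** The Primary Outcome section of the protocol article leads with "continued abstinence from smoking since the end of the treatment period, i.e., 6 months sustained abstinence" and qualifies it as "with no relapse (defined as 7+ days of continuous smoking, and no reported smoking in the last week", followed by biochemical verification at 8 months. It then names the instrument: "Sustained abstinence will be assessed via the following question", namely "When did you last smoke a cigarette, even a puff". Referral for CO testing depends on that report: "If a participant reports prolonged abstinence at the 8 month follow up, and no smoking in the last week". A reading of 8 ppm or higher counts as recent smoking.

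Other places use short labels for the same endpoint:
- Abstract: "The primary outcome is 6 months continuous abstinence from end of treatment with biochemical verification".
- Table 1: "6 month prolonged abstinence (primary outcome".
- Sample Size Determination: "for the primary outcome of prolonged abstinence at 8 months", with assumed rates of 1% vs 8%.

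The Secondary Outcomes section lists further smoking items at 2, 5 and 8 months: 7-day point prevalence, consumption, quit attempts by duration, and when smoking first resumed after a quit attempt. The article does not link any of these to the primary outcome.

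**The concern.** The rule needs to know whether any smoking since the end of treatment ran for 7 or more consecutive days. The named question returns one date, that of the last puff. The two do not match, and they stand a sentence apart in the same section.

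Two things are at stake. First, lapsers could be scored contrary to the stated rule: failed when it accepts them, or passed when it excludes them. Second, CO testing is offered only to those judged to report prolonged abstinence. If staff apply a strict reading at the interview, a lapser whom the rule accepts is never tested. No later choice of definition can restore that missing verification.

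The parenthesis adds a separate drafting fault. Read literally, not having smoked in the last week is part of what relapse means.

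**Working it through.** **1. Rule against instrument.** Table 2 puts treatment in weeks 1 to 8 and the 8-month assessment at week 34. Sort participants by their answer to the last-puff question:

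| Last puff | Strict reading | 7-day rule | Determined by the question? |
|---|---|---|---|
| Before end of treatment | Success, subject to CO | Success, subject to CO | Yes |
| Within the last 7 days | Failure | Failure | Yes |
| After end of treatment, but more than 7 days ago | Failure | Depends on the length of any smoking run | No under the 7-day rule |

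Example for the third row: two participants both answer three months ago. One took a single puff; the other smoked daily for ten days. The strict reading fails both. The 7-day rule passes the first and fails the second. Their answers are identical.

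CO cannot separate them, because the article defines a positive reading as a sign of recent smoking only.

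**2. Can other items fill the gap?** Only in part. If first and last smoking dates are less than 7 days apart, a 7-day run is ruled out. If they are further apart, a run is neither confirmed nor excluded. No listed item records consecutive smoking days.

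**3. The plan's own sample size.** Inputs from Sample Size Determination: 1% vs 8%, 80% power, p = 0.05 (taken as two-sided), 30% attrition. Unpooled normal approximation:

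n = (1.960 + 0.842)² × (0.01×0.99 + 0.08×0.92) / 0.07² = 7.849 × 0.0835 / 0.0049 = 133.8, so 134 per arm.

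134 / 0.70 = 191.4, stated as 191 per arm. The arithmetic reproduces. Expected successes are 134 × 0.01 = 1.3 and 134 × 0.08 = 10.7.

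**4. Sensitivity to reclassification.** Two-sided Fisher exact p, 134 per arm (illustrative; the planned analysis is a logistic mixed model with cluster effects):

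| Control vs intervention | p |
|---|---|
| 1 vs 11 (about the expected counts) | 0.005 |
| 1 vs 10 | 0.010 |
| 1 vs 9 | 0.019 |
| 1 vs 8 | 0.036 |
| 1 vs 7 | 0.066 |
| 2 vs 10 | 0.034 |
| 2 vs 9 | 0.060 |

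From 1 vs 11, four intervention successes must be lost, with none lost in control, before p exceeds 0.05. One reclassification is enough only if the counts already sit at a boundary such as 1 vs 8 or 2 vs 10.

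**5. Sensitivity of power to the definition.** The article gives no rates by definition, so every pair except the first is an assumption. With n = 134 per arm and p̄ the mean of p₁ and p₂:

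power = Φ{[(p₂ − p₁)√n − 1.96√(2p̄(1 − p̄))] / √(p₁(1 − p₁) + p₂(1 − p₂))}

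- 1% vs 8%: (0.8103 − 0.5746) / 0.2890 = 0.816, power 79%.
- 1% vs 6% (strict scoring lowers the intervention rate): 61%.
- 2% vs 8% (lenient scoring raises only the control rate): 62%.
- 2% vs 10% (lenient scoring raises both rates): 79%.

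The definition can matter to power, but need not.

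**The case against.** The strongest defence is that the Primary Outcome section holds the only operational rule. The Abstract gives a short label, and no part of the article states a competing rule that a single puff means failure. A reader might infer two incompatible endpoint definitions; the text does not support that. Continuous, sustained and prolonged are loose names, and the real conflict is between rule and question within one section.

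The affected group is also limited to the third row of the first table. A reader might infer that the endpoint as a whole cannot be classified, but the first two rows are settled under either reading.

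The interviews at 2, 5 and 8 months help as well. Someone who smoked daily until three months before the last call would usually have reported current smoking at 5 months. This narrows the gap but does not close it, because those items are not assigned to the primary outcome and do not record runs of smoking days.

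A reader might also infer that one reclassified participant decides the trial. At the expected counts that is not so.

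Nor is bias towards one arm shown. Assessors are blinded, and the question is the same in both arms. Strict scoring from the last puff would be a demanding endpoint applied equally.

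Finally, an analysis plan not shown here may say how answers map to success. It could choose a definition, but it could not supply run lengths or CO readings that were never collected.

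**Conclusion.** The point holds as a mismatch between a stated rule and its stated instrument. The last-puff question cannot apply the 7-day rule to participants who smoked after the end of treatment and then stopped more than a week before the 8-month call. Their scoring and their referral for CO testing are left to discretion. The misplaced condition in the parenthesis is a clear drafting error. The differing labels in the Abstract, Table 1 and Sample Size Determination add to the ambiguity but are secondary.

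The size is unknown, since the documents do not say how many participants would fall in the undetermined group. With roughly a dozen successes expected in total, a handful of reclassifications could alter the result. That statement rests on the plan's 1% and 8% rates, 134 evaluable participants per arm and simple Fisher tests that ignore clustering. The sample size arithmetic is sound, but the article does not say which definition its rates describe. Correction is warranted because this is the primary endpoint, missed CO tests cannot be recovered, and the repair is cheap.

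**What to change.** State one definition in the Abstract, Table 1, Primary Outcome and Sample Size Determination. Rewrite the parenthesis so that no smoking in the last week is a condition for success. Then choose one of two routes:

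- **(a) Strict.** Success means that the last puff was before the end of the treatment period and CO is below 8 ppm. Delete the 7-day rule. The existing question is then sufficient.
- **(b) Lapse-tolerant.** Keep the 7-day rule. Add one direct follow-up item asking whether the participant has smoked on 7 or more consecutive days since the end of treatment. Send for CO testing everyone who meets the rule and has not smoked in the last week.

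In either case, say which definition the 1% vs 8% assumption refers to. The cost is a wording amendment and, under (b), one interview item plus CO visits for the additional participants who qualify.

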### Participant Recruitment and Retention

Peer workers will visit sites and provide information to both staff and potential participants about the study to encourage recruitment. Service staff will be asked to refer potential participants (at any stage of their treatment) to the study via the peer worker. Additional recruitment strategies will be by advertising (e.g., flyers, newsletters, online via service websites) and peer workers attending community meetings and other events to inform potential participants directly about the study to encourage self-referral.

For those who meet eligibility criteria and decide to participate in the study, the peer worker will gain written informed consent from the participant. Provision is made on the consent form for opting in or out of possible participation in a qualitative study of experiences of trying to stop smoking and for participation in further studies.

Telephone follow-up and compensation for completed assessments will aid in increasing retention rates. Monthly check-in texts (to remind participants to inform the researchers if their contact details change) will be conducted to help maintain contact with participants, and 3 monthly follow-up will assist with accurate participant recall of smoking and quitting history. Participants will receive a $40 gift card for baseline and for each completed follow-up assessment and a $40 gift card for the 8-month face-to-face assessment for biochemical verification of self-reported smoking cessation (if required).

Upon completion of the baseline assessment, the peer worker will provide standard smoking care (described above) to all participants. The peer worker will then access the randomization allocation for the participant via the eCRF program, and communicate appropriately with the participant.

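### The stated assessment of six-month abstinence rests on a month-8 last-cigarette date and gives no rule for a contradictory 5-month smoking report

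*Protocol article*

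**What the plan says.** All references are to the Protocol article.

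- **Definition (Primary Outcome).** The outcome is "continued abstinence from smoking since the end of the treatment period, i.e., 6 months sustained abstinence". A relapse clause then qualifies it: "with no relapse (defined as 7+ days of continuous smoking, and no reported smoking in the last week". A CO check at the 8-month contact completes the definition.
- **Instrument (same section).** "Sustained abstinence will be assessed via the following question"; the item asks for the date of the most recent cigarette, down to a single puff.
- **CO test (same section).** The trigger is "If a participant reports prolonged abstinence at the 8 month follow up, and no smoking in the last week". Such participants are invited to an in-person CO test, and the cut-off is "a reading of 8 ppm or higher defined as indicative of recent smoking".
- **Schedule (Table 1, smoking measures).** The row "6 month prolonged abstinence (primary outcome)" is marked at 8 months only. The row "7 day point prevalence abstinence (self-reported)" is marked at 2, 5 and 8 months. Current smoking and quit attempts are recorded at baseline and at all three follow-ups.
- **Role of the interim reports (Secondary Outcomes).** The 2- and 5-month smoking data are listed as secondary outcomes.
- **Purpose of the contacts (Participant Recruitment and Retention).** "3 monthly follow-up will assist with accurate participant recall of smoking and quitting history".
- **Timing (Table 2).** The cessation program ends at week 8. Follow-ups are at weeks 9, 21 and 34.

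**The concern.** The definition covers six months, but the named assessment looks back over all of it from one interview at the end. The last-week criterion and the CO reading describe only the period just before month 8. Whether the participant was abstinent around month 5 therefore rests on a recalled date.

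The trial holds better evidence on that point: a blinded interview at week 21 that asks about current smoking. The article does not say that this report is compared with the month-8 answer. An analyst who programmed the Primary Outcome section as it stands would use month-8 data alone.

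At stake is an endpoint with very few expected events. False successes at a similar rate in both arms would dilute the contrast. If over-reporting were more common among participants who know they received support, it would inflate the contrast.

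**Working it through.** **1. Where the interviews fall.** The window runs from week 8 to week 34, which is 34 − 8 = 26 weeks.
- Week 21 is 21 − 8 = 13 weeks into the window and 34 − 21 = 13 weeks before its end, so it lies in the middle.
- Week 9 is one week into the window. Its 7-day recall covers only the first week, so it is at the edge and carries little of the argument.

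**2. Test records, assuming at week 34 no smoking in the last week and CO below 8 ppm.**

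| Record | Outcome definition | Stated month-8 assessment |
|---|---|---|
| Daily smoker at week 21; at week 34 gives a last-cigarette date at most 13 weeks back (truthful) | Fails | Fails: the date is about 3 months back, short of 6 |
| Daily smoker at week 21; at week 34 misdates the last cigarette to seven months ago; CO 3 ppm | Fails | Passes |
| Lapse of under 7 continuous days around week 21 | Allowed by the relapse wording | Depends on how the last-puff answer is read |

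Only the second row is the defect described here.

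**3. The plan's own sample size.** Inputs from Sample Size Determination: 1% vs 8%, 80% power, p = 0.05 (two-sided assumed), 134 per arm, about 30% attrition.
- n = (1.96 + 0.8416)² × (0.01×0.99 + 0.08×0.92) / 0.07² = 133.8, so 134 per arm. This reproduces the plan.
- 134 / 0.7 = 191.4, given as 191 per arm. The point does not challenge these figures.

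**4. Expected successes.** 134 × 0.01 = 1.3 and 134 × 0.08 = 10.7.

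**5. Illustrative sensitivity to false successes.** The rates are assumed. Power is for the pooled two-proportion z test at 134 per arm by exact binomial enumeration, ignoring clustering.

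| Points added to both arms | Rates | Risk ratio | Power |
|---|---|---|---|
| 0 | 1% vs 8% | 8.0 | 84% |
| 0.5 | 1.5% vs 8.5% | 5.7 | 79% |
| 1 | 2% vs 9% | 4.5 | 75% |
| 2 | 3% vs 10% | 3.3 | 66% |

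The normal approximation starts lower, at 79%, and falls in the same way. In counts, 1 vs 11 successes of 134 gives p = 0.003 and 4 vs 11 gives p = 0.063 (same test).

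**6. The opposite case.** Suppose the planned 1% and 8% already contain recall error, and a cross-check removes a share of successes in both arms.

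| Share removed | Rates | Power |
|---|---|---|
| 10% | 0.9% vs 7.2% | 79% |
| 20% | 0.8% vs 6.4% | 74% |
| 30% | 0.7% vs 5.6% | 67% |

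The check can therefore cost power relative to the plan, depending on what the planning rates include.

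**The case against.** The strongest reply has four parts.

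- **The sentence about the 8-month report says who is invited for CO testing; it is not a scoring rule.** This is right. The definition comes earlier in the section, and a daily smoker at week 21 does not meet it. But the section also names the last-cigarette question as the way sustained abstinence is assessed, and nothing in the article links the definition to the week-21 record.
- **The article is condensed and no analysis plan is shown.** A reader might infer that the trial ignores the interim reports, or that success depends on recall alone. The documents support neither. No section excludes the interim reports, the 3-monthly contacts are given a role in aiding recall, and the last-week and CO criteria also apply. What stands is narrower: the stated method is specific down to the question wording and the CO cut-off, and as stated it can pass a record that the definition rejects.
- **Most month-5 smokers would not slip through.** A reader might infer that anyone smoking at month 5 can count as a success. A truthful last-cigarette date exposes the relapse, and a lapse under 7 continuous days is permitted. The defect is limited to misdated recall by someone who has stopped by month 8.
- **The size is unknown.** This is also right. Two points added to both arms would put false control successes at twice the planned control rate. Participants are not told of the comparison condition, which reduces differential over-reporting but does not remove it.

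A related weakness is separate: a date of last puff cannot tell a permitted lapse from a 7-day relapse.

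**Conclusion.** The point holds in limited form. The stated assessment can count as a success a participant whose own blinded week-21 interview shows a relapse inside the window, if that participant misdates the last cigarette at month 8. Neither the last-week criterion nor CO at month 8 can correct this.

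How often it would happen cannot be derived from the documents, so the tables show sensitivity and are not estimates. They rest on assumed error rates, 134 evaluable per arm, a two-sided 5% test and no clustering. The firm part is that about a dozen events are expected in total, so moving a few can change the conclusion. This is an inexpensive improvement to the derivation. It does not show that the planned result is biased.

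**What to change.** Add to the Primary Outcome section:

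1. The primary outcome also requires that the available 5-month smoking report does not show a relapse as the protocol defines it, for example current daily smoking at week 21. Daily smoking is a proxy for the 7-day rule, so the criterion should be written out in terms of the items asked.
2. A missed 5-month interview does not by itself cause failure.
3. The number of records in which the 5- and 8-month answers conflict is reported by arm.

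Settle this before unblinding, because a later choice could alter a result resting on so few events.

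The cost is a short wording change and some derivation code, using data already scheduled for all participants. There are two downsides. There will be slightly fewer successes, which could lower power if the planned 1% and 8% already include recall error. The check is also unavailable for those who missed the 5-month call.

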#### Secondary Outcomes

##### Smoking

Secondary outcomes assessed at 2-, 5-, and 8-months post baseline will include:
7-day point prevalence abstinence, based on “Have you smoked at least part of a cigarette in the last 7 days?”Reported cigarettes smoked per day (for daily smokers) or cigarettes per week (for non-daily smokers).Expenditure on cigarettes.Number of quit attempts of 24 h or more, 1 week or more, and 1 month or more in the previous 3 months or since last assessed.Time to relapse: in those who do relapse will be determined by asking when they first smoked after a quit attempt.Number of subsequent quit attempts among those who relapsed.Hospitalizations and other intensive health service use.Financial stress questions adapted from Siahpush and Carlin (46).Productivity impacts (time off work or other duties).

Heaviness of Smoking Index (HSI): Nicotine dependence is assessed using this two item Index (47, 48). It uses a six-point scale calculated from the number of cigarettes smoked per day (1–10, 11–20, 21–30, 31+) and the time to first cigarette after waking (≤5, 6–30, 31–60, and 61+ min). Nicotine dependence is then categorized into a three-category variable: low (0–1), medium (2–4), and high (5–6). The HSI has been found to have good reliability and reasonable predictive validity (49).

Cravings: assessed by one item taken from the International Tobacco Control (ITC) Four Country Survey (50, 51), “Currently, how often do you get strong cravings to smoke tobacco?” with the response options of: (1) Hourly or more often; (2) Several times per day; (3) At least once a day; and (4) Less than daily. Difficulty in coping with situations in which smoking is not allowed is also assessed, on a 4-point Likert Scale from “very,” “moderately,” “mildly” to “not at all difficult.”

Withdrawal symptoms: as assessed by the Minnesota Nicotine Withdrawal Scale [MNWS; (52)], an eight item ordinal scale rating withdrawal symptoms from 0 (not present) to 3 (severe). At baseline the MNWS is administered, with two symptoms (concentration and appetite) assessed at follow-up. The MNWS has been shown to have good reliability and predictive validity (53).

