##### Substance use

The Alcohol Use Disorders Identification Test—Brief [AUDIT-C; (40)] a three item screening tool used to identify hazardous alcohol use or active alcohol use disorders. It is scored on a scale of 0–12 with a cut off of 3 (women) or 4 (men). For men, it has been shown to have a sensitivity of 0.90 and specificity of 0.45; for women the sensitivity is 0.80, and specificity is 0.87.

The Cannabis Use Disorders Identification Test—Revised [CUDIT-R; (42)] is a briefer (8-item) and more refined version of the CUDIT (55), a simple modification of the AUDIT. Items cover the domains of consumption, cannabis problems, dependence, and psychological features. The CUDIT-R was found to comprise a single factor, with high test-retest reliability (*r* = 0.871), high internal consistency (α = 0.914), and discriminant validity (area under the curve = 0.960). Only question 1, “How often do you use cannabis? (over the last 2 months)” is included in the present study (never, monthly or less, 2 to 4 times a month, 2 to 3 times a week, 4 or more times a week). In addition, participants who use cannabis are asked “Do you ever mix tobacco with your cannabis?” with response options of “Yes, always or nearly always,” “Yes, sometimes” or “No, never or very rarely.”

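### Both abstinence questions ask only about cigarettes, so a participant who still smokes tobacco mixed with cannabis can truthfully be recorded as abstinent

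*Protocol article*

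**What the plan says.** Under Primary Outcome, the protocol article defines the endpoint as "continued abstinence from smoking since the end of the treatment period, i.e., 6 months sustained abstinence". Relapse is defined as at least 7 days of continuous smoking, and there must also be no smoking in the last week. Sustained abstinence is measured by one printed question, "When did you last smoke a cigarette, even a puff". Participants who report prolonged abstinence and no smoking in the last week are invited to a face-to-face CO test, "with a reading of 8 ppm or higher defined as indicative of recent smoking".

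Under Secondary Outcomes (Smoking), 7-day point prevalence abstinence rests on "Have you smoked at least part of a cigarette in the last 7 days". Table 1 lists this outcome as self-reported and places CO testing at 8 months only, in those who report abstinence.

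Under Substance use, cannabis users are asked "Do you ever mix tobacco with your cannabis". Table 1 schedules this item at baseline and at 2, 5 and 8 months. The row "Tobacco types" is scheduled at baseline only. The eligibility criteria do not exclude cannabis users.

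**The concern.** The outcome is abstinence from smoking, but both abstinence questions are about cigarettes. The trial expects that some participants will smoke tobacco in another form, since it asks about mixing at every assessment. No stated rule uses that answer to classify abstinence. In a single interview a participant could report no cigarette in the past week and also report nearly always mixing tobacco with cannabis. The protocol does not say how to class that person, and the cigarette question alone would class them as abstinent.

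What is at stake is false successes. On the 7-day outcome nothing stands behind the self-report. On the primary outcome the CO test does, but it is a single reading that the protocol itself treats as a marker of recent smoking. The planned number of primary events is very small, so each misclassified participant carries weight.

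**Working it through.** **1. The texts side by side**

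| Element | Scope | Tobacco mixed with cannabis covered? |
|---|---|---|
| Primary outcome definition | smoking | not stated |
| Sustained-abstinence question | a cigarette | no |
| 7-day question (2, 5, 8 months) | part of a cigarette | no |
| Cravings item | smoking tobacco | wider wording |
| Mixing item (baseline and all follow-ups) | tobacco in cannabis | yes, but not used in any outcome |
| CO test (8 months, reported abstainers) | recent smoking | only if the reading is 8 ppm or higher |

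The two abstinence questions are narrower than the outcome they measure. The cravings item shows that the trial uses the wider term elsewhere.

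**2. Where a false success can arise**

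- *7-day outcome:* any mixed use in the last week is missed, with no biochemical check.
- *Primary outcome, last-week condition:* the condition is worded as smoking, but both printed abstinence questions name a cigarette. Mixed use in that week is missed unless the CO reading reaches 8 ppm.
- *Primary outcome, earlier months:* occasional mixed use need not amount to 7 continuous days of smoking, so under the protocol's own relapse rule it is not clearly a failure.

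**3. The planned event count**

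Inputs from Sample Size Determination: 1% vs 8%, 80% power, p = 0.05 (taken as two-sided), 134 per arm, 30% attrition.

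The plan's figure reproduces with the unpooled formula:

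n = (1.960 + 0.842)² × (0.01 × 0.99 + 0.08 × 0.92) / 0.07² = 133.75, so 134 per arm. Then 134 / 0.7 = 191.4, stated as 191 per arm, or 382 in total.

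Expected events: 134 × 0.01 = 1.3 and 134 × 0.08 = 10.7, or about 1 vs 11.

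**4. Sensitivity to a few misclassified participants**

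Two-sided Fisher exact test, 134 per arm. This is an illustration; the planned analysis is a mixed logistic model with clustering. The counts moved are assumptions.

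| Scenario | Intervention vs control events | p |
|---|---|---|
| Expected | 11 vs 1 | 0.005 |
| One false success in each arm | 12 vs 2 | 0.011 |
| Two false successes in each arm | 13 vs 3 | 0.018 |
| One intervention event lost | 10 vs 1 | 0.010 |
| Two lost | 9 vs 1 | 0.019 |
| Three lost | 8 vs 1 | 0.036 |
| Four lost | 7 vs 1 | 0.066 |
| Two false successes in controls only | 11 vs 3 | 0.051 |
| One false success in controls, two intervention events lost | 9 vs 2 | 0.060 |

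The rows with 1 to 3 lost events correspond to an assumed 10% to 30% of 11 events.

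**5. Sensitivity of power**

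Let f be an assumed share of true smokers counted as abstinent, equal in both arms. The observed rate is then p + (1 − p)f. At f = 1% this gives 0.01 + 0.99 × 0.01 = 1.99% and 0.08 + 0.92 × 0.01 = 8.92%. With the pooled normal approximation at 134 per arm, power is 79% at f = 0, then 75%, 71%, 63% and 57% at f = 0.5%, 1%, 2% and 3%.

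**The case against.** Several points on the other side stand.

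- Participants enter as smokers of at least 10 cigarettes a day, roll-your-own tobacco is ordinarily a cigarette, and some people would call a mixed joint one. Interviewer prompts may sit in case report forms that are not shown. The printed wording is nevertheless what the article fixes, and an item that can be read either way is itself a reason to be explicit.
- The relapse rule weakens the case for the primary outcome. A reader might infer that any mixed tobacco smoked during the 6 months makes a false success. The protocol does not support that: use on a few occasions a month, outside the last week, would not clearly be relapse even if the tobacco were in cigarettes.
- CO testing protects the primary outcome in part. Someone who recently smoked mixed tobacco and reads 8 ppm or higher is not counted as abstinent.
- A reader might also infer that the CO rule wrongly fails people who smoke cannabis without tobacco. The documents do not say that cannabis smoke raises breath CO or how long a reading stays raised, so this remains an assumption. Counting every reading at or above the cut-off as failure is a defensible conservative rule.
- A reader might infer that the misclassification would overturn the trial's result. The table does not show that. Within the assumed range of 1 to 3 lost events, and with one or two false successes in each arm, p stays below 0.05. Crossing it takes four lost events, errors confined to the control arm, or both errors acting together against the intervention.

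**Conclusion.** The point holds as a gap between the outcome and its measurement. As written, the plan can record a current smoker of tobacco mixed with cannabis as abstinent. This is clearest for the self-reported 7-day outcome and next for the last-week condition of the primary outcome, where one CO reading is a partial check. The trial already collects an answer that exposes the conflict and states no use for it.

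The size cannot be derived from the documents. They give neither the prevalence of cannabis use or mixing nor the share of such participants who would read below 8 ppm. The p-values and power figures above are a range under assumed rates; they are not an estimate of bias and do not show that the conclusion would change. The correction is worth making because it is cheap and because answers given to the narrower question cannot be fully recovered later.

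**What to change.** - At 2, 5 and 8 months, word both abstinence items as any smoked tobacco, including roll-your-own, cigar, pipe or tobacco mixed with cannabis, even a puff.
- State that tobacco mixed with cannabis counts as smoking, and apply the protocol's own relapse rule and last-week condition to it exactly as to cigarettes.
- Keep a CO reading of 8 ppm or higher as failure in the primary analysis.
- Optionally, add a short item at the CO visit on how recently and by what route cannabis was used. It would support one prespecified sensitivity analysis of self-reported tobacco abstainers who read 8 ppm or higher. The existing items cannot: they cover frequency over 2 months and whether tobacco is ever mixed in, and give neither route nor timing relative to the test.

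The cost is two reworded questions and, if the sensitivity analysis is wanted, one short item and one table. Reported abstinence may be slightly lower, and comparison with studies that used cigarette-only wording becomes less literal.
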